## Abstract

**Background:**

Patellofemoral pain is a prevalent knee condition affecting up to 40% of individuals, especially females aged teens to 50 s. Standard treatments, including exercise therapy, often yield insufficient long-term results, partly due to low compliance and psychological factors like depression and catastrophizing of pain. A digital therapeutics “MORA Cure PFP,” which combines structured progressive exercise and cognitive behavioral therapy via an app, offers a solution to overcome the limitations of conventional treatment for patellofemoral pain patients.

**Methods:**

To evaluate the safety and efficacy of MORA Cure PFP, a two-arm controlled trial will enroll 216 patients diagnosed with patellofemoral pain randomly assigned in a 1:1 ratio to treatment and control groups. The treatment group will use the app, while the control group will perform self-guided exercises using educational materials. This trial aims to determine if the treatment group shows greater reduction in usual pain intensity scores at 8 weeks compared to the control group. Additional assessments include worst pain, knee function, depression, and pain catastrophizing levels.

**Discussion:**

Key design elements of the clinical trial, such as control group selection, inclusion/exclusion criteria, number of patients, and primary endpoint, were designed with consideration for not only medical perspectives but also regulatory aspects of software as a medical device, including device approval and health technology assessment.

**Trial registration:**

ClinicalTrials.gov., NCT06260865, registered 15th February 2024.

**Supplementary Information:**

The online version contains supplementary material available at 10.1186/s13063-025-09030-2.

## Administrative information

Note: the numbers in curly brackets in this protocol refer to SPIRIT checklist item numbers. The order of the items has been modified to group similar items (see http://www.equator-network.org/reporting-guidelines/spirit-2013-statement-defining-standard-protocolitems-for-clinical-trials/).

## Introduction

### Backgroundand rationale {6a}

Patellofemoral pain (PFP) is a common condition with a prevalence ranging from 3 to 40% [1], accounting for 25% of knee pain originating from running [2] and 7 to 10% of all medical consultations [3, 4]. It is more prevalent in females and affects individuals from their teens to their 50 s [1, 3]. The pathophysiology of PFP remains unclear [5], and various non-surgical and surgical treatments have been attempted [6, 7]. Without proper diagnosis and treatment, PFP does not improve spontaneously [8]; over 50% of patients may experience persistent pain for more than 2 years [9], potentially leading to the progression of patellofemoral osteoarthritis [10].

Standard treatment for PFP, according to various guidelines, includes patient education and exercise therapy [11–14]. Strength exercises targeting the quadriceps and hip abductors have proven effective in several studies [15–21]. However, even with evidence-based treatments, 40 to 57% of patients experience insufficient long-term effects [22, 23], highlighting the need for improved therapeutic strategies. Low compliance due to time and location constraints of clinic-based exercise therapy may contribute to this lack of effectiveness [24].

Psychological factors such as anxiety, depression, catastrophizing, and fear of movement are associated with pain and physical function in PFP patients and negatively impact recovery processes like rehabilitation training, as suggested by Maclachlan’s systematic review [25]. To address these factors, Selhorst et al. conducted a randomized controlled trial with adolescent PFP patients, comparing rehabilitation training alone to rehabilitation combined with stepwise cognitive intervention. The group receiving multidisciplinary intervention showed significant improvements in pain and functional levels [26]. Similarly, Bagheri et al. found that young female athletes participating in a mindfulness program alongside exercise exhibited better outcomes in pain severity, knee function, subjective treatment effects, and catastrophizing compared to those who only engaged in exercise [27]. Despite these findings, research on psychological interventions in PFP patients remains limited [26–30], and no studies have combined CBT, which has proven efficacy in chronic pain [31, 32], with exercise therapy in PFP patients.

App-based therapy can overcome time and location constraints of face-to-face treatment, thereby improving patient compliance [33, 34]. EverEx has developed a multidisciplinary treatment app “MORA Cure PFP” for PFP patients that includes self-rehabilitation exercise therapy, which automatically adjusts based on the patient’s status, and CBT for chronic pain. MORA Cure PFP is classified as a software as a medical device (SaMD) that can only be used after diagnosis and prescription by a physician and is prior to regulatory approval. An exploratory clinical trial involving 40 patients, conducted from November 2022 to October 2023 (ClinicalTrials.gov., NCT05614583) demonstrated efficacy and safety comparable to real-world treatment [35].

### Objectives {7}

This confirmatory clinical trial aims to evaluate the safety and efficacy of MORA Cure PFP by comparing it with conventional treatment in PFP patients. For specific objectives, see Table 1.

**Table 1 Tab1:** Objectives and efficacy endpoints of the trial

Objectives	Endpoints
**Primary** To compare usual pain level at 8 weeks between treatment and control group	Usual pain intensity over the past 1 week at the 8-week (V4)
**Secondary** To compare the following between treatment control group: 1. Worst pain level at 8-week 2. Knee function at 8-week 3. Quality of life at 8-week 4. Health status at 8-week 5. Depression level at 8-week 6. Pain catastrophizing level at 8-week 7. Overall perceived recovery level at 8-week 8. Usual pain at 12-week 9. Worst pain level at 12-week 10. Knee function at 12-week 11. Quality of life at 12-week 12. Health status at 12-week 13. Depression level at 12-week 14. Pain catastrophizing level at 12-week 15. Overall perceived recovery level at 12-week 16. Usual pain level at 4-week 17. Worst pain level at 4-week 18. Knee function at 4-week 19. Change in usual pain level at 8-week compared to baseline 20. Change in worst pain level at 8-week compared to baseline 21. Change in knee function at 8-week compared to baseline 22. Change in quality of life at 8-week compared to baseline 23. Change in health status at 8-week compared to baseline 24. Change in depression level at 8-week compared to baseline 25. Change in pain catastrophizing level at 8-week compared to baseline 26. Change in usual pain level at 12-week compared to baseline 27. Change in worst pain level at 12-week compared to baseline 28. Change in knee function at 12-week compared to baseline 29. Change in quality of life at 12-week compared to baseline 30. Change in health status at 12-week compared to baseline 31. Change in depression level at 12-week compared to baseline 32. Change in pain catastrophizing level at 12-week compared to baseline 33. Change in usual pain level at 4-week compared to baseline 34. Change in worst pain level at 4-week compared to baseline 35. Change in knee function at 4-week compared to baseline	1. Worst pain intensity over the past 1 week at 8-week (V4) 2. Kujala questionnaire total score at 8-week (V4) 3. EQ-5D-5L questionnaire total score at 8-week (V4) 4. EQ-5D-5L questionnaire health status score at 8-week (V4) 5. PHQ-9 questionnaire total score at 8-week (V4) 6. PCS questionnaire total score at 8-week (V4) 7. Overall perceived recovery score at 8-week (V4) 8. Usual pain intensity over the past 1 week at 12-week (V5) 9. Worst pain intensity over the past 1 week at 12-week (V5) 10. Kujala questionnaire total score at 12-week (V5) 11. EQ-5D-5L questionnaire total score at 12-week (V5) 12. EQ-5D-5L questionnaire health status score at 12-week (V5) 13. PHQ-9 questionnaire total score at 12-week (V5) 14. PCS questionnaire total score at 12-week (V5) 15. Overall perceived recovery score at 12-week (V5) 16. Usual pain intensity over the past 1 week at 4-week (V2) 17. Worst pain intensity over the past 1 week at 4-week (V2) 18. Kujala questionnaire total score at 4-week (V2) 19. [Usual pain intensity over the past 1 week at the 8-week (V4)] – [Usual pain intensity over the past 1 week at the baseline (V2)] 20. [Worst pain intensity over the past 1 week at the 8-week (V4)] – [Worst pain intensity over the past 1 week at the baseline (V2)] 21. [Kujala questionnaire total score at the 8-week (V4)] – [Kujala questionnaire total score at the baseline (V2)] 22. [EQ-5D-5L questionnaire total score at the 8-week (V4)] – [EQ-5D-5L questionnaire total score at the baseline (V2)] 23. [EQ-5D-5L questionnaire health status score at the 8-week (V4)] – [EQ-5D-5L questionnaire health status score at the baseline (V2)] 24. [PHQ-9 questionnaire total score at the 8-week (V4)] – [PHQ-9 questionnaire total score at the baseline (V2)] 25. [PCS questionnaire total score at the 8-week (V4)] – [PCS questionnaire total score at the baseline (V2)] 26. [Usual pain intensity over the past 1 week at the 12-week (V5)] – [Usual pain intensity over the past 1 week at the baseline (V2)] 27. [Worst pain intensity over the past 1 week at the 12-week (V5)] – [Worst pain intensity over the past 1 week at the baseline (V2)] 28. [Kujala questionnaire total score at the 12-week (V5)] – [Kujala questionnaire total score at the baseline (V2)] 29. [EQ-5D-5L questionnaire total score at the 12-week (V5)] – [EQ-5D-5L questionnaire total score at the baseline (V2)] 30. [EQ-5D-5L questionnaire health status score at the 12-week (V5)] – [EQ-5D-5L questionnaire health status score at the baseline (V2)] 31. [PHQ-9 questionnaire total score at the 12-week (V5)] – [PHQ-9 questionnaire total score at the baseline (V2)] 32. [PCS questionnaire total score at the 12-week (V5)] – [PCS questionnaire total score at the baseline (V2)] 33. [Usual pain intensity over the past 1 week at the 4-week (V3)] – [Usual pain intensity over the past 1 week at the baseline (V2)] 34. [Worst pain intensity over the past 1 week at the 4-week (V3)] – [Worst pain intensity over the past 1 week at the baseline (V2)] 35. [Kujala questionnaire total score at the 4-week (V3)] – [Kujala questionnaire total score at the baseline (V2)]

### Trial design {8}

This clinical trial is a confirmatory medical device clinical trial and is a two-arm, 1:1 randomized, open-label, multi-centered superiority study. Participants who meet the inclusion/exclusion criteria will be randomly assigned to the treatment group and the control group. Treatment group will be given the digital therapeutic app, and control group will receive exercise education and self-exercise materials. Participant flow diagram according to the Consolidated Standards of Reporting Trials (CONSORT), is presented in Fig. 1.

**Fig. 1 Fig1:**
[figure not shown]
CONSORT flow diagram

## Methods: participants, interventions, and outcomes

### Study setting {9}

This clinical trial will be conducted at both academic hospitals and community hospitals (for the list of sites, see https://clinicaltrials.gov/study/NCT06260865) located in South Korea. After being diagnosed and receiving the guidance on the intervention at the hospital, participants will perform the treatment themselves on a daily basis.

### Eligibility criteria {10}

To be included in this study, patients must meet the following criteria: experiencing pain around or behind the patella (kneecap) in unilateral or bilateral knee joints for over 3 months [15, 16, 36]; pain during squatting movements [13, 15–17, 19, 36–39]; pain in two or more of the following activities/tests—prolonged sitting, cycling, running, climbing stairs, kneeling, patellar compression test, tenderness around the patella test [13, 15–17, 19, 36–39]; voluntary decision to participate with signed informed consent.

Exclusion criteria are as follows: knee osteoarthritis exceeding Kellgren-Lawrence (K-L) grade 2 on X-ray [36]; traumatic event causing fractures or dislocations around the knee within the past 3 months [15, 19]; knee surgery within the past 3 months [16, 17, 37, 38]; patellar tendinitis diagnosed by imaging within the past 3 months [37]; current use of narcotic analgesics for pain control [16, 39]; anticipated use of prohibited medications/treatments within 16 weeks of screening; pregnancy; current or recent (within 3 months) participation in another clinical trial; and any other factors deemed unsuitable by the investigator [36].

### Who will take informed consent? {26a}

Before participating in the clinical trial procedures, participants will voluntarily complete and sign an informed consent form. The consent form will be paper-based, and a licensed physician will explain its contents, giving the participant sufficient time to make an informed decision. The consent of the research participants must be obtained in accordance with the ethical principles and standards outlined in the Declaration of Helsinki. All consent forms used will be those approved by the IRB, and a copy of the signed consent form will be provided to the participant. If the consent form is amended, the changes will be explained, and the consent process will be repeated.

### Additional consent provision for collection and use of participant data and biological specimens {26b}

There will be no attempt to retain or request permission from participants to use the data gathered in this study for additional research purposes. No supplementary studies are planned.

This trial does not collect biological specimens.

## Interventions

### Explanation for the choice of comparators {6b}

To evaluate the safety and efficacy of MORA Cure PFP, the treatment group was assigned to use the app. The control group was set as the real-world at best treatment. Standard treatment for PFP, according to various guidelines, includes patient education and exercise therapy [11–14]. Therefore, the control group was defined as those who receive in-person exercise education by healthcare professionals, follow the provided paper-based materials to perform self-exercise, and record their exercise progress.

### Intervention description {11a}

After confirming eligibility based on the inclusion/exclusion criteria, the target knee (left or right) for evaluation will be selected. If only one knee meets the criteria for PFP, that knee will be selected. If both knees qualify, the knee with greater pain will be chosen. All subsequent evaluations will be conducted on the knee selected as the target knee for assessment.

The investigational medical device “MORA Cure PFP” used in this study will be applied only to participants assigned to the treatment group. MORA Cure PFP consists of a web platform for healthcare professionals and a mobile application for patients. The investigator prescribes treatment through the healthcare web platform, and participants install the application on their mobile phones to begin therapy. At baseline, the investigator will randomize and enroll participants. For those assigned to the treatment group, the investigator will register them on the healthcare web platform and prescribe the device. Upon prescription, an installation code for the patient app will appear on the web platform. Participants will then follow the installation manual to install the app, agree to the terms of service, complete registration, and start the plan, with the Day 1 program beginning on the same day. The device provides an 8-week program of rehabilitative exercise and cognitive behavioral therapy (CBT) for PFP (Fig. 2). After the initial 8-week treatment period, participants can retain access to the device for up to 12 weeks.

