### Confidentiality {27}

The investigator must ensure the anonymity of study participants, avoiding any identification of participants’ names in documents submitted to the sponsor. Signed consent forms, source documents, and participant logs must be kept confidential and stored securely. All personal information collected through the investigational device follows personal information processing policy, and participants shall consent before installing the app.

Data collection systems in this trial comply with US code of federal regulation chapter 21, part 11 and local regulations. All data transmissions are encrypted, and access is controlled through individual user IDs and passwords, with only authorized and trained personnel permitted access.

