## Statistical methods

### Definition of analysis sets

In this clinical trial, data will be analyzed using three sets: the full analysis set (FAS), the per protocol set (PPS), and the safety set. The FAS, aligned with the intention-to-treat (ITT) principle, will be the primary analysis set for efficacy evaluations, with additional analyses using the PPS. If discrepancies arise between the two, the outcomes will be presented and investigated. Safety evaluations will use the safety set.

The FAS includes participants who meet all of the following: have post-randomization primary efficacy data, records of applying the investigational device (test group) or performing self-exercise (control group), and were not improperly enrolled due to inclusion/exclusion violations. The PPS is a subset of the FAS, including those who completed the trial without major protocol violations, did not withdraw prematurely, and had an overall compliance rate of 50% or higher. The safety set includes all randomized participants with records of using the investigational device or performing self-exercise.

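### A usable phone and willingness to use the app are not entry criteria; they are tested after randomisation in the app arm only, and the full analysis set then drops those who cannot start

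*Protocol article*

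**What the plan says.** Eligibility criteria {10} opens its inclusion list with "To be included in this study, patients must meet the following criteria". The list covers duration and site of pain, pain on squatting, pain in at least two further activities or tests, and signed consent. The exclusions concern the knee, medication and treatment, pregnancy and other trials, and end with "any other factors deemed unsuitable by the investigator". A phone, the ability to run the app and acceptance of its terms do not appear.

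Intervention description {11a} states that, in the app arm, "participants install the application on their mobile phones to begin therapy". It also gives the order of events. Eligibility is confirmed first. Then: "At baseline, the investigator will randomize and enroll participants". Only after that: "For those assigned to the treatment group, the investigator will register them on the healthcare web platform and prescribe the device". The participant next has to "install the app, agree to the terms of service, complete registration, and start the plan". Confidentiality {27} adds a personal-information step: "participants shall consent before installing the app". Controls receive in-person teaching, paper material and a paper diary, none of which needs a phone.

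Definition of analysis sets makes the FAS the primary efficacy set and describes it as following the intention-to-treat principle. One of its conditions is "records of applying the investigational device (test group) or performing self-exercise (control group". The safety set has a similar record condition. Sample size {14} applies a single 20% dropout rate to both groups.

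**The concern.** Whether a patient has a phone that runs the app, and is willing to use it, is settled before allocation and is equally common in both arms under randomisation. The plan lets it act only after allocation and only in the app arm. Two people alike in this respect are therefore treated differently. The one allocated to the app cannot start, generates no device record and is removed from the primary analysis, even if the 8-week pain score is available. The one allocated to control exercises from paper and is kept.

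The arms compared in the FAS are then no longer the arms that were randomised. If people who cannot or will not use the app have a different pain outcome from the rest, the difference between groups is shifted by something other than treatment.

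**Working it through.** **Plan's own figure.** With d = 0.428, two-sided alpha 0.05 and power 0.80: n = 2(1.960 + 0.842)² / 0.428² = 85.7, so 86 per group. 86 / 0.8 = 107.5, so 108 per group and 216 in total. The stated figures reproduce, and the point does not touch that arithmetic.

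**Inputs.** From Sample size {14}: 108 per arm, 20% dropout, and exploratory results of 2.31 (SD 1.49) and 3.18 (SD 2.43). Root-mean-square SD = √[(1.49² + 2.43²)/2] = 2.016, so d = 0.87 / 2.016 = 0.432 from the printed values. The plan's 0.428 comes from unrounded data; using it lowers the powers below by less than one percentage point. For example, with no extra loss, 0.428 × √(86.4/2) − 1.960 = 0.853, which is 80.3% instead of 81.0%.

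**Assumptions (not in the documents).** p is the share of participants who could not or would not start the app. k is the difference in 8-week pain, in SD units, between them and the others.

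**Removal, which is what the FAS rule does.** The app arm has 108(1 − p) × 0.8 evaluable and the control arm 108 × 0.8 = 86.4. Power = Φ(0.432 / √(1/n_app + 1/n_control) − 1.960), ignoring the negligible far tail.

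| p | Non-starters of 108 | n app | n control | Power |
|---|---|---|---|---|
| 0 | 0 | 86.4 | 86.4 | 81.0% |
| 2% | 2.2 | 84.7 | 86.4 | 80.6% |
| 5% | 5.4 | 82.1 | 86.4 | 80.0% |
| 10% | 10.8 | 77.8 | 86.4 | 78.9% |

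**Selection.** The app-arm mean without non-starters differs from the mean of everyone randomised to that arm by p × k SD. The control arm keeps its counterparts, so the group difference shifts by the same p × k. With no true effect, let λ = pk / √(1/n_app + 1/n_control). Two-sided type I error = 1 − Φ(1.960 − λ) + Φ(−1.960 − λ).

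| p | k | Shift (SD) | Type I error |
|---|---|---|---|
| 2% | 0.5 | 0.010 | 5.05% |
| 2% | 1.0 | 0.020 | 5.2% |
| 5% | 0.5 | 0.025 | 5.3% |
| 5% | 1.0 | 0.050 | 6.2% |
| 10% | 0.5 | 0.050 | 6.2% |
| 10% | 1.0 | 0.100 | 9.8% |

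Worked case, p = 10% and k = 0.5: λ = 0.05 / √(1/77.8 + 1/86.4) = 0.05 × 6.40 = 0.32, and 1 − Φ(1.64) + Φ(−2.28) = 0.0505 + 0.0113 = 6.2%. That shift is 0.05 / 0.432 = 12% of the planned effect. It favours the app if non-starters would have had more pain, and counts against it if less.

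**Retention as untreated, which the plan does not do.** If non-starters gain nothing over control, the effect is 0.432(1 − p). With 86.4 per arm, power is 79.4%, 76.9% and 72.4% at 2%, 5% and 10%. This matters only for judging the fix.

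**The case against.** The number affected may be small. The article condenses a full protocol that is not shown and that may contain a handset requirement. A physician explains the trial before consent, so someone set against a phone app can decline. The discretionary exclusion could be used for a candidate with no usable phone. Installation is a scheduled baseline step supported by a manual and instruction. The 20% dropout allowance was drawn from trials of digital services and may already cover some failure to start. All of this lowers the likely count. None of it is a stated check applied equally to both arms before allocation, and discretion can vary between sites.

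Three stronger readings are tempting and are not supported.

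- A reader might infer that only the app arm can lose participants from the FAS. Controls also need a self-exercise record, which is a paper diary collected where feasible, so they can drop out of the set too. The one-sidedness holds for this cause only.
- A reader might infer that power falls to about 72% at a 10% rate. That assumes non-starters are kept as untreated, whereas the FAS rule removes them.
- A reader might infer that the personal-information consent is also sought only after randomisation. Confidentiality {27} says only that it precedes installation. It is the installation and the in-app terms that are placed after allocation.

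It can also be said that the bias originates in the FAS definition. That is correct: with every randomised participant kept, a missing phone would only dilute the effect. The fix therefore has to change that definition as well as the entry criteria.

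**Conclusion.** The point holds as a structural fault of probably modest size. Taken together, the entry criteria, the order of steps and the FAS record condition remove participants from the app arm after randomisation for a cause that cannot operate in the control arm.

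The cost in power is minor, from about 81% to 79% at an assumed 10% rate. The cost in validity depends on two quantities that the documents do not give: the share who cannot or will not start, and how far their pain differs. At 2% it is negligible, and with a 0.5 SD difference it is small at 5% and noticeable at 10%. Only the more extreme assumption of 10% and 1 SD brings type I error close to 10%. The change is worth making because it is inexpensive and removes a known departure from the randomised comparison, not because a large bias has been shown.

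**What to change.** 1. In Eligibility criteria {10}, add an inclusion criterion, confirmed for every candidate before randomisation in the IWRS: possession of a phone that meets the app's requirements, and stated willingness to use the app and accept its terms if allocated to it. Controls need not accept the terms themselves.
2. In Definition of analysis sets, remove the condition on a record of use or self-exercise as a route out of the primary analysis, so that randomised participants are analysed in their assigned arm whether or not they started. Report non-starters by arm.

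Recruitment opened on 26 April 2024 and was expected to finish by the end of December 2024, so the first change helps only those not yet randomised. The second still applies to everyone already enrolled.

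Cost: an amendment needing IRB and MFDS approval, an updated consent form with repeat consent where it changes, and a few extra screen failures among people who could not use the device. Any remaining non-starters would dilute the effect slightly; at 2% the power is 79.4% against 81.0%. Results would apply to phone users willing to use the app, who are the only people able to use it.
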